### **Interim Analysis**

Because this is a feasibility pilot study, formal interim analyses are not needed.

## **7.3 Subject Population(s) for Analysis**

For both the primary and secondary analyses, we will use the all-treated population and as a sensitivity analysis the set of subjects who completed at least 80% of 10 tDCS sessions.

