#### **Feasibility**

We define feasibility as 70% of eligible patients choosing to enroll in the study. Other feasibility parameters will include willingness of clinicians to refer and help recruit patients, number of eligible participants, willingness of participants to enroll, retention of patients, and completeness of data collection.

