#### **Acceptability**

We define acceptability as 80% of study participants completing 80% of the 10-session tDCS treatment protocol. We will also ask participants about their satisfaction, perceptions, and experiences with the tDCS treatments. Other acceptability parameters will include rates of adherence to tDCS protocol, dropout rates and reasons for non-completion.

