#### **Tolerability**

We define tolerability as an overall tolerability rating of "very tolerable." This will be a self-report based on a global question "Considering all aspects of your experience, how would you rate the overall tolerability of the tDCS intervention?" The response options are: very tolerable, somewhat tolerable, neutral, somewhat intolerable, and very intolerable. We will ask this question after the last tDCS session. Other tolerability parameters will include the tDCS adverse effects questionnaire.

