### **4.3 Subject Recruitment, Enrollment and Screening**

To ensure representativeness of an inpatient population, potential subjects will be recruited from both GE3W (Mood Disorders Unit where patients typically have TRD) and GE3E (Medical Psychiatric and Geriatric Psychiatric Unit where patients either have medical-psychiatric conditions or are older adults 65 years and older) inpatient units. Other than age requirement of 18 years or older and ability to provide informed consent, patients who meet inclusion criteria and are willing to participate will be enrolled regardless of sex and gender, race, or ethnic group and social determinants.

Study coordinators will review Epic for daily admissions to the inpatient units to pre-screen for eligibility. When a potential subject is identified, the study coordinators will review with the PI or Co-Investigator for appropriateness, and then ask permission from the primary inpatient treatment team consultant or providers to approach the patient. With the primary service's permission, the study coordinator will explain the study to the patient, answer questions about the study, and enroll and obtain written informed consent from the patient.

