### **4.4 Early Withdrawal of Subjects**

#### **4.4.1 When and How to Withdraw Subjects**

Subjects will be withdrawn from the study prior to completing study procedures in the following circumstances:

- Subject decision to withdraw from the study (withdrawal of consent)
- Subject inability to adhere to protocol requirements
- Severe adverse effects (SAEs) requiring medical intervention
- If the investigators determine it is in the best interest of the subject

There are no anticipated risks particular to early or abrupt discontinuation of tDCS. If subjects discontinue tDCS treatments or withdraw early and require ongoing medical treatment, appropriate referrals will be arranged. Should a subject experience any medical emergency during participation in a study visit, whether related to the study or not, the subject will be evaluated by clinical on-call inpatient psychiatric staff.

If an enrolled subject withdraws from the study prior to completion, an attempt will be made to enroll another subject in order to achieve the target enrollment.

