#### Primary Hypothesis:

**Hypothesis 2.1:** We hypothesize that the proposed 5-day tDCS treatment protocol will be feasible (enrollment of 70% of eligible patients), acceptable (80% of study participants completing 80% of the 10-session tDCS treatments) and tolerable (overall tolerability rating of "very tolerable" by self-report) to implement in the inpatient psychiatric setting.

Percentage of subjects completing the study and adhering to the protocol will be reported.

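### Section 7.3 applies the all-treated and ≥80%-completer sets to the primary endpoints, which conflicts with the denominators that define feasibility and acceptability

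*Protocol*

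**What the plan says.** Section 7.3 of the protocol names the analysis sets in one sentence. The main set: "For both the primary and secondary analyses, we will use the all-treated population". The second: "as a sensitivity analysis the set of subjects who completed at least 80% of 10 tDCS sessions". No endpoint is exempted. Section 7.2 uses the label primary for Hypothesis 2.1, which covers feasibility, acceptability and tolerability, so 7.3 reaches all three.

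Section 3.2 defines the endpoints with denominators of their own. Feasibility: "We define feasibility as 70% of eligible patients choosing to enroll in the study". Acceptability: "We define acceptability as 80% of study participants completing 80% of the 10-session tDCS treatment protocol". Tolerability is a single global self-rating after the last session, and the target is the top category. The objective in 2.1 and the primary hypothesis in 7.2 repeat the feasibility and acceptability criteria with the same denominators.

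Two other provisions bear on who is counted. When a subject withdraws, section 4.4.1 says "an attempt will be made to enroll another subject in order to achieve the target enrollment". Section 4.4.2 keeps the data collected before withdrawal in the analyses.

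**The concern.** A proportion is informative only if its analysis set can contain both those who meet the criterion and those who do not. Two of the pairings in 7.3 break this rule.

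- **Acceptability in the ≥80% set.** The rule for entering the set is the endpoint itself.
- **Feasibility in the all-treated set.** Everyone in the set has enrolled. The eligible patients who declined, whose number the endpoint is meant to reveal, cannot be in it.

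A third pairing changes the denominator without making the result trivial. Acceptability is defined on study participants, and 4.3 places consent and enrolment before any treatment. The all-treated set drops those who consent and leave before session 1.

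The trial's primary question is whether the study can be done, and these proportions are its main product. With a target of 10 subjects, one person in or out of a denominator can decide whether a threshold is met.

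**Working it through.** **Inputs.** Feasibility threshold 70% of eligible patients (2.1, 3.2, 7.2). Acceptability threshold 80% of participants, each with at least 0.80 × 10 = 8 sessions (3.2). Target accrual 10 (7.1). Analysis sets as in 7.3. The protocol gives no expected number of eligible patients, untreated subjects or completers; the values below are assumptions to show the range. There is no calculated figure in the protocol on this point to reproduce, since 7.1 does without a power calculation.

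**Step 1: acceptability in the ≥80% set.** Let n be the number treated and k the number of these with at least 8 sessions. The main analysis gives k/n. The sensitivity set has exactly those k members, so it gives k/k.

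| k of n = 10 | Main analysis | ≥80% set |
|---|---|---|
| 3 | 3/10 = 30% | 3/3 = 100% |
| 7 | 7/10 = 70% (fails) | 7/7 = 100% |
| 8 | 8/10 = 80% (meets) | 8/8 = 100% |

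The result is 100% for every k from 1 to 10, so this analysis cannot test the robustness of the main one.

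**Step 2: feasibility.** With E eligible patients and 10 enrolled, section 3.2 gives 10/E. The target needs 10/E ≥ 0.70, so E ≤ 10/0.70 = 14.3, that is, at most 14. If all 10 are treated, the all-treated set gives 10/10 whatever E is.

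| Assumed E | Definition in 3.2 | All-treated set |
|---|---|---|
| 12 | 10/12 = 83% (meets) | 100% |
| 14 | 10/14 = 71% (meets) | 100% |
| 15 | 10/15 = 67% (fails) | 100% |
| 20 | 10/20 = 50% (fails) | 100% |
| 40 | 10/40 = 25% (fails) | 100% |

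**Step 3: acceptability in the main set.** Suppose one subject consents, leaves before session 1 and is replaced, so that 11 consented and 10 were treated.

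| Completers | All-treated | All consented |
|---|---|---|
| 7 | 7/10 = 70% (fails) | 7/11 = 64% (fails) |
| 8 | 8/10 = 80% (meets) | 8/11 = 73% (fails) |
| 9 | 9/10 = 90% (meets) | 9/11 = 82% (meets) |

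The verdict turns only in the middle row. If instead 10 is the number consented and nobody is replaced, one untreated subject does not turn it (7/9 = 78% against 7/10 = 70%, both fail; 8/9 = 89% against 8/10 = 80%, both meet). Two can: 7/8 = 88% meets, 7/10 = 70% fails.

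**Step 4: tolerability.** Neither set is selected on the rating, so the result can vary in both. The ≥80% set merely leaves out those who stopped early.

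**The case against.** The strongest reply is that the feasibility denominator is fixed as eligible patients in 2.1, 3.2 and 7.2, and that 7.3 is a general sentence which no sensible analyst would apply to an enrolment rate. Much of this stands. A reader might infer that feasibility is certain to be declared met. The protocol does not support that, because an analyst who follows 3.2 obtains a proportion that can fail. What remains is a contradiction between 7.3 and 3.2. The reply does not help the sensitivity analysis of acceptability, which is circular on any reading that applies 7.3 to the primary endpoints.

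The loss before session 1 may also be rare: section 6 places consent, baseline tests and the first session in the same visit. The schedule of events, however, lets baseline precede treatment 1 by up to 72 hours, so such a loss is possible. Its rate is unknown. Dropout is to be reported in any case, so these subjects would not vanish from the report, only from the denominator.

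Three stronger readings are tempting and do not hold.

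- **Replacement removes failures.** With three replaced withdrawals one might contrast 10/13 = 77% with 10/10. But subjects who were treated and then withdrew are in the all-treated set by definition, and 4.4.2 keeps their data. Only those who leave before session 1 are lost.
- **Patients whose treating team refuses an approach leave the denominator.** Section 4.3 requires staff to "ask permission from the primary inpatient treatment team consultant or providers to approach the patient", but 4.1 and 4.2 do not make that permission an eligibility criterion, and 3.2 tracks clinicians' willingness to refer separately. Whether someone never offered the study can be said to have chosen is a question of definition, not an error.
- **Enrolment and tolerability will not be estimated.** The reporting sentence in 7.2 reads "Percentage of subjects completing the study and adhering to the protocol will be reported", but it follows a restatement of all three criteria. Details of estimation, including intervals, may be left to a statistical analysis plan.

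**Conclusion.** The point holds as a mismatch between the sets in 7.3 and the endpoint definitions in 3.2. The ≥80% sensitivity analysis of acceptability is 100% by construction and tells the reader nothing. Feasibility computed in the set that 7.3 names would be 100%, against 25% to 83% under the definition in 3.2 if 12 to 40 patients were eligible (an assumed range). The main acceptability analysis uses a narrower denominator than its definition. At this sample size one untreated subject can move it across the threshold (80% against 73%), though only near the boundary and only if such a subject occurs.

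The main acceptability result and tolerability are not predetermined, and the sets in 7.3 are reasonable for the pre-post measures. In a single-arm pilot of this size the matter should be fixed before analysis, but it does not make the trial unable to answer its question.

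**What to change.** Amend 7.3 so that each primary endpoint has its own denominator:

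- **Feasibility:** all patients meeting 4.1 and 4.2 who are identified in the daily admission screening of 4.3, logged as they occur.
- **Acceptability:** all consented subjects, with those never treated and those withdrawn before reaching 8 sessions counted as not completing, whether or not they are replaced.
- **Tolerability:** name the denominator. Only treated subjects can rate the treatment, and nothing here argues against using all of them.

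Keep the all-treated set and the ≥80% set for the exploratory pre-post outcomes (called secondary in 7.2), and state that the ≥80% set is not used for acceptability.

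The cost is a few sentences. The daily review of admissions already supplies the list of eligible patients, provided that the count is kept prospectively. The reported rates may come out slightly less favourable.

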## 8 Safety and Adverse Events

Monitoring for adverse events will be conducted during study period. Subjects will be administered tDCS Adverse Effects questionnaire after each treatment and at post-treatment assessment. Overall incidence of all AEs and SAEs, as well as incidence of specific AEs and SAEs, will be determined.

### 8.1 Definitions

#### Unanticipated Adverse Device Effect (UADE)

A UADE is any serious adverse effect on health or safety or any life-threatening problem or death caused by, or associated with, a device if that effect, problem or death was not previously identified in nature, severity, or degree of incidence in the investigational plan, or any other unanticipated serious problem associated with a device that relates to the rights, safety, or welfare of subjects.

#### Adverse Effect (Event)

Any untoward medical occurrence in a subject involved in clinical study of an investigational device; regardless of the causal relationship of the problem with the device or, if applicable, other study related treatment(s).

**Associated with the investigational device:** There is a reasonable possibility that the adverse effect may have been caused by the investigational device.

**Life-threatening adverse effect:** Any adverse effect that places the subject, in the view of either the investigator or the sponsor, at immediate risk of death from the effect **as it occurred**. It does not include a reaction that, had it occurred in a more severe form, might have caused death.

**Serious adverse effect:** An adverse effect is considered “serious” if, in the view of either the investigator or the sponsor, it results in any of the following outcomes:

- death
- a life-threatening AE
- inpatient hospitalization or prolongation of existing hospitalization
- a persistent or significant disability/incapacity
- a congenital anomaly/birth defect.

**Unanticipated adverse effect:** Any adverse effect, the nature, specificity, severity, or frequency of which is not consistent with the risk information in the clinical study protocol.

#### General Physical Examination Findings

At screening, any clinically significant abnormality should be recorded as a preexisting condition. At the end of the study, any new clinically significant findings/abnormalities that meet the definition of an adverse event must also be recorded and documented as an adverse event.

### **Hospitalization, Prolonged Hospitalization or Surgery**

Any adverse event that results in hospitalization or prolonged hospitalization (outside of the current psychiatric hospitalization) should be documented and reported as an unanticipated adverse device effect unless specifically instructed otherwise in this protocol. Any condition responsible for surgery should be documented as an adverse event if the condition meets the criteria for an adverse event.

Neither the condition, hospitalization, prolonged hospitalization, nor surgery are reported as an adverse event in the following circumstances:

- *Hospitalization or prolonged hospitalization for diagnostic or elective surgical procedures for a preexisting condition. Surgery should **not** be reported as an outcome of an adverse event if the purpose of the surgery was elective or diagnostic and the outcome was uneventful*
- *Hospitalization or prolonged hospitalization required to allow efficacy measurement for the study*
- *Hospitalization or prolonged hospitalization for therapy of the target disease of the study, unless it is a worsening or increase in frequency of hospital admissions as judged by the clinical investigator. (This is anticipated to apply to all of our subjects who are hospitalized with TRD and can have prolonged hospitalization as indicated clinically.)*

### **Post-Study Adverse Event**

All unresolved adverse events should be followed by the investigator until the events are resolved, the subject is lost to follow-up, or the adverse event is otherwise explained. At the last scheduled visit, the local investigator should instruct each subject to report, to the local investigator, any subsequent event(s) that the subject, or the subject's personal physician, believes might reasonably be related to participation in this study.

### **Preexisting Condition**

A preexisting condition is one that is present at the start of the study. A preexisting condition should be recorded as an adverse event if the frequency, intensity, or the character of the condition worsens during the study period.

### **Unanticipated Problems Involving Risk to Subjects or Others (UPIRTSO)**

Any unanticipated problem or adverse event that meets all of the following three criteria:

- **Serious:** Serious problems or events that results in significant harm, (which may be physical, psychological, financial, social, economic, or legal) or increased risk for the subject or others (including individuals who are not research subjects). These include: (1) death; (2) life threatening adverse experience; (3) hospitalization - inpatient, new, or prolonged; (4) disability/incapacity - persistent or significant; (5) birth defect/anomaly; (6) breach of confidentiality and (7) other problems, events, or new information (i.e. publications, DSMB reports, interim findings, product labeling change) that in the opinion of the local investigator may adversely affect the rights, safety, or welfare of the subjects or others, or substantially compromise the research data, **AND**
- **Unanticipated:** (i.e., unexpected) problems or events are those that are not already described as potential risks in the protocol, consent document, not listed in the Investigator's Brochure, or not part of an underlying disease. A problem or event is "unanticipated" when it was unforeseeable at the time of its occurrence. A problem or event is "unanticipated" when it occurs at an increased frequency or at an increased severity than expected, **AND**
- **Related:** A problem or event is "related" if it is possibly related to the research procedures.

### **Adverse Event Reporting Period**

For this study, the study treatment period is defined as immediately following the last administration of tDCS treatment and post-tDCS assessments.

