### **3.4 Primary Safety Endpoints**

Monitoring for adverse events will be conducted during study period. Subjects will be asked to complete the tDCS Adverse Effects questionnaire after each tDCS treatment. Overall incidence of all AEs and SAEs, as well as incidence of specific AEs and SAEs, will be determined.

The tDCS adverse effects questionnaire lists 12 possible tDCS side effects and asks a participant to rate whether they experienced any on a 4-point Likert scale (ranging from 1 - absent to 4 - severe), and to what extent they attribute each side effect to tDCS (ranging from 1 - not at all to 4 - completely).[11]

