## **6 Study Procedures**

### **Overview of the tDCS intervention:**

Upon enrollment, the subject will receive tDCS treatments for 30 minutes twice daily, at least 30 minutes apart. During the tDCS treatments, the subject will remain in their room, be seated in a comfortable position, and instructed to sit quietly with their eyes open throughout the procedures. The left dorsolateral prefrontal cortex (L-DLPFC) position will be established in relation to external cephalic landmarks. The electrode cables will be connected to the tDCS stimulator, placed on the scalp, with the anode (connected to the stimulator by the red cable) centered on the marked L-DLPFC reference point and the

cathode (connected to the stimulator by the black cable) over the right supraorbital area. (Figure 4)

Subjects will receive a total of 10 tDCS treatments over 5 days. Before and after the course of 10 tDCS treatments, subjects will complete depression questionnaires, cognitive testing, and EEG. Only personnel trained in tDCS will perform the treatments. tDCS operators will be present throughout the entirety of all tDCS treatments to ensure that effective tDCS is delivered and adjust current intensity for subject comfort. Safety monitoring will be done before and after each twice daily treatments to assess for adverse effects. Personnel will be trained in using the CGX wireless EEG and NIRSIT. This study will leverage existing equipment (tDCS and EEG units) from the Mayo Clinic Depression Center and emerging infrastructure of the Minnesota Precision Neuromodulation Center (Min PeNCe) provided by a Minnesota Partnership Grant.

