### **Visit 1 - Baseline Assessment visit\***

The baseline visit can take up to 2 hours and will include the following:

The **Study Coordinator** will complete:

- Enrollment and consent process
- Collect physical examination from the medical records
- Adverse Events/Serious Adverse Events forms

The **Subject** will complete:

- Montgomery-Asberg Depression Rating Scale (MADRS)
- Snaith-Hamilton Pleasure Scale (SHAPS)
- Cognitive questionnaires
  - Adverse Childhood Experiences (ACE)
  - Premorbid intelligence quotient (pIQ)
  - Wide Range Achievement Reading Test (WRART)
  - Socioeconomic Status (SES)
  - Stroop Test
  - Revised Hopkins Verbal Learning Test (HVLT-R)
  - Digital Symbol Coding Test (DSCT)

- Wireless EEG with recording
  - The wireless EEG procedure will take up to 40 minutes to complete, including 15-20 minutes of EEG recording, and up to 10 minutes before and after recording for set up and removal of EEG cap.
- fNIRS with the NIRSIT device
  - The brain imaging acquisition will take 5-10 minutes to complete, including placing the device over the head and completing a verbal fluency test for a few minutes.
- tDCS treatments (2 30-minute sessions)
  - The tDCS treatment will take up to 40 minutes to complete each time, including 30 minutes of brain stimulation, and up to 5 minutes before and after stimulation for set up and removal of device.
  - There are 2 tDCS sessions per day, with each session at least 30 minutes apart.

\*tDCS treatment #1 starts during the baseline visit.

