| fNIRS (NIRSIT)                                    |                                              | X                                                       |                     | X                                                               |
| tDCS (2 mA, 30 min)                               |                                              |                                                         | X                   |                                                                 |
| PHQ-9 (from EMR)                                  | X                                            |                                                         |                     |                                                                 |
| MADRS                                             |                                              | X                                                       |                     | X                                                               |
| Cognitive assessments (Stroop, HVLT-R, DSCT)      |                                              | X                                                       |                     | X                                                               |
| Other Assessments (ACE, premorbid IQ, SES, WRART) |                                              | X                                                       |                     |                                                                 |
| Device Interrogation Save to Disk                 |                                              |                                                         |                     |                                                                 |
| Concurrent Medications                            |                                              | X                                                       |                     |                                                                 |
| Adverse Events                                    |                                              |                                                         | X                   | X                                                               |
| Serious Adverse Events                            |                                              |                                                         | X                   | X                                                               |

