## **8.2 Recording of Adverse Events**

At each contact with the subject, the investigator must seek information on adverse events by specific questioning and, as appropriate, by examination. Study subjects will be routinely questioned about adverse effects at study visits. Information on all adverse events should be recorded immediately in the source document, and also in the appropriate adverse event section of the case report form (CRF) or in a separate adverse event worksheet. All clearly related signs, symptoms, and abnormal diagnostic, laboratory or procedure results should be recorded in the source document.

All adverse events occurring during the study period must be recorded. All observed or volunteered adverse effects (serious or non-serious) and abnormal test findings, regardless of the treatment group if applicable or suspected causal relationship to the investigational device or if applicable other study treatment or diagnostic product(s) will be recorded in the subjects' case history. For all adverse effects sufficient information will be pursued and/or obtained as to permit; an adequate determination of the outcome, an assessment of the causal relationship between the adverse effect and the investigational device or, if applicable other study treatment or diagnostic product. The clinical course of each event should be followed until resolution, stabilization, or until it has been ultimately determined that the study treatment or participation is not the probable cause. Serious adverse events that are still ongoing at the end of the study period must be followed up, to determine the final outcome. Any serious adverse event that occurs after the study period and is considered to be at least

possibly related to the study treatment or study participation should be recorded and reported immediately.

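### The adverse-event reporting period has no start and, read literally, falls after treatment; the side-effect questionnaire has no rating before the first session

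*Protocol*

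**What the plan says.** **Reporting period.** Protocol Section 8.1, Adverse Event Reporting Period, consists of one sentence, which says that "the study treatment period is defined as immediately following the last administration of tDCS treatment and post-tDCS assessments". No start is given.

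**Collection during treatment.** Section 8 says "Monitoring for adverse events will be conducted during study period", and Section 8.2 says "All adverse events occurring during the study period must be recorded". The visit descriptions in Section 6 list "Adverse Events/Serious Adverse Events forms" at Visit 1, and list the same forms at the treatment visits and the post-treatment visit. The Schedule of Events marks adverse events and serious adverse events in the Treatment Visits column (Visits 1-10) and in the post-treatment column.

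**Questionnaire.** Section 3.4 says "Subjects will be asked to complete the tDCS Adverse Effects questionnaire after each tDCS treatment". Sections 8 and 10.1 add one administration at the post-treatment assessment. The form has 12 items. Each is rated on a four-point severity scale that begins at absent, and on a four-point scale for how far the patient attributes the effect to tDCS. No administration before the first session is specified.

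**Pre-session check and pre-existing symptoms.** The overview in Section 6 says "Safety monitoring will be done before and after each twice daily treatments to assess for adverse effects", without naming an instrument. Under Section 8.1, a preexisting condition "should be recorded as an adverse event if the frequency, intensity, or the character of the condition worsens during the study period".

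**The concern.** The incidence of all and of specific adverse events is the primary safety endpoint (Section 3.4). Two things bear on how it can be read.

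First, the boundary of the reporting period decides what must be recorded. Inside the study period, Section 8.2 requires every adverse event. After it, Section 8.2 requires only serious events at least possibly related to the treatment or to participation. Section 8.1 is the only place that tries to set the boundary, and it does so for a differently named period (study treatment period rather than study period).

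Second, the effects listed in Section 1.4.2 include headache, fatigue, nausea, and mood or sleep changes. Patients admitted for severe depression can have these before any stimulation, and Section 5.5 allows psychotropic changes during the course. With no comparator and no earlier rating on the same items, a post-session report cannot be separated from a symptom the patient already had.

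**Working it through.** The protocol states no adverse-event rate, target or decision rule, so there is no figure to reproduce. The check is a comparison of passages, a count, and an illustration on stated assumptions.

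**1. Reporting period against collection.**

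| Place | When events are collected |
|---|---|
| 8.1 Adverse Event Reporting Period | No start; literally, after the last session and assessments |
| 3.4 | Questionnaire after every session |
| 6, visit descriptions | Forms at Visit 1, treatment visits and post-treatment visit |
| Schedule of Events | Visits 1-10 and post-treatment |
| 8 and 10.1 | Study period; questionnaire after every session and at post-treatment |
| 8.2 | All events in the study period |

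Only the first row leaves out the treatment course. The end is also loose: Section 6 places the post-treatment visit on the day of treatment 10, while the schedule allows up to 72 hours after it.

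**2. What the literal window would hold.** Planned questionnaires per patient: 10 after sessions + 1 at post-treatment = 11. At most the form after session 10 and the post-treatment form follow the last session: 2/11 = 18%. If the session-10 form is not counted, 1/11 = 9%. The forms after sessions 1-9 fall outside on any literal reading. This measures the contradiction; it does not predict what would be reported.

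**3. Ratings before stimulation.** Sections 3.4, 8 and 10.1 agree on the questionnaire's timing, and none places it before session 1. Three further passages show why that matters:
- Section 1.4.2 summarises a review of 209 tDCS studies as finding no difference in adverse-event rates between active and sham. On the protocol's own evidence, raw reports are therefore not a measure of device effect.
- Section 8.2 (Causality and Severity Assessment) classes events of unknown and questionable relationship as device-associated for reporting, so ambiguous symptoms lean toward tDCS.
- No passage says how an item rating becomes an adverse event.

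**4. Illustration.** Let q be the chance that an item is reported after a session with no tDCS effect. The protocol gives no value; 5% and 10% are assumed. The share of patients reporting the item at least once over 10 sessions depends on how strongly reports cluster within patients.

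| Assumed q | Full persistence: q | Independent sessions: 1 - (1 - q)^10 |
|---|---|---|
| 5% | 5% (0.5 of 10 patients) | 1 - 0.95^10 = 40% (4.0 of 10) |
| 10% | 10% (1.0 of 10 patients) | 1 - 0.90^10 = 65% (6.5 of 10) |

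Pre-existing symptoms would tend to persist, which favours the lower end. The documents do not place the true value within the range.

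**The case against.** The strongest reply is that the defect in Section 8.1 is one of wording. The sentence may be a garbled end point, and every operative passage collects events during treatment. That stands. A reader might infer that adverse-event incidence will in fact be taken from the wrong window, but the documents do not support this: the questionnaire timing, the forms and the schedule all cover the sessions.

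A reader might also infer that the schedule leaves Visit 1 unmarked, because its Baseline column is blank for adverse events. It does not. The Treatment Visits column is headed Visits 1-10, and treatment 1 is part of Visit 1.

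Nor is it right that the worsening rule cannot be applied. Medical history at screening (Sections 5.5 and 6), recording of abnormalities as preexisting (Section 8.1, General Physical Examination Findings), the check before each treatment, and specific questioning at each contact (Section 8.2) all give it some basis. What they lack is an earlier rating on the same four-point items.

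Finally, Section 8.1 defines an adverse event regardless of cause, attribution is rated separately, and the primary tolerability measure is a single global question (Section 3.2). So it cannot be said that background symptoms will be counted as tDCS effects. But attribution is the patient's own opinion in an open-label study, and no stated rule brings it into the incidence. An SAP, which is not shown, could define new-or-worse counting, but it could not supply a baseline rating that was never collected.

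**Conclusion.** The point holds in two limited parts. The reporting-period definition is wrong as written: it has no start, literally excludes treatment, and must be reconciled with Sections 3.4, 6, 8 and 8.2 and the schedule. Separately, the absence of a pre-stimulation questionnaire means that item-level incidence may include symptoms that were already there. That this will happen, and by how much, is not shown.

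The 5-10% to 40-65% range rests wholly on assumed background rates and on the degree of clustering within patients. The upper end should not be quoted alone, since independence between sessions sits badly with persistent symptoms. Nor do the documents support the inference that nearly every patient would report something across the 12 items: the items are not listed and their background rates are unknown.

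The change is worth making because it is cheap and a missed baseline cannot be recovered. The three primary endpoints (feasibility, acceptability and global tolerability) are not affected.

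**What to change.** 1. Replace the sentence in Section 8.1 with a period that has a start and an end: from the first study procedure through the post-treatment assessment. Use the same term there and in Section 8.2, and agree the end with the post-treatment visit description and the schedule's 72-hour allowance.
2. Give the same 12-item questionnaire once before session 1, and add it to Visit 1 in Section 6 and to Sections 3.4, 8 and 10.1.
3. For each item, report three results side by side: raw incidence, incidence of ratings that are new or worse than the pre-session-1 rating, and the attribution ratings.

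The cost is one sentence for the period, matching edits where the questionnaire timing is stated, and one short form for each of 10 patients. No extra visit is needed, because treatment 1 already takes place at Visit 1.
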